**Fig. 1 Fig1:**
[figure not shown]
Participant flow consort

**Fig. 2 Fig2:**
[figure not shown]
Schedule for enrolment, intervention, and assessments for the trial. OGTT, 2-h 75 g Oral Glucose Tolerance Test; BIA, Bioelectrical impedance analysis, SF-36, short-form health survey; STAI, The Stare-Trait Anxiety Inventory; BDI-II, Beck Depression Inventory; CERQ, Cognitive Emotion Regulation Questionnaire; MEQ, Morningness-Eveningness Questionnaire; PSQI, The Pittsburgh Sleep Quality Index; SHS, Subjective Happiness Scale; HLQ, Health Literacy Questionnaire; PSS-4, Perceived Stress Scale 4; WHO-5, World Health Organization Wellbeing Index; BISQ-R-SF, Brief Infant Sleep Questionnaire-Revised Short Form; CSHQ, Children’s Sleep Habits Questionnaire; StimQ toddler/preschool, Cognitive Home Environment Questionnaire; ASQ-3, Ages & Stages Questionnaires-3; BRIEF-2, Behaviour Rating Inventory of Execute Functions-2; BASC-3-BESS Parent Form, Behavioral and Emotional Screening System; PHQ-4, Patient Health Questionnaire; IPAQ-SF, The International Physical Activity Questionnaire- Short Form; MFFQ, Modified Food Frequency Questionnaire

### Sample size {14}

#### Expected number of participants

The sample size is estimated based on the cumulative diabetes risk identified from the GUSTO study [12]. We assume groups of equal size, with a significance level of 0.05% and a power of 80%. Additionally, we consider a median survival time of 6 years for the non-intervention group (based on GUSTO data), a follow-up period of 3 years, and an expected 50% reduction in the risk of developing T2D for the intervention group (hazard ratio = 0.5). These assumptions yield a cumulative event rate of 0.22 for the comparison group and 0.12 for the intervention group. Considering a 20% censoring rate, we calculate a sample size of 189 for the intervention group and 188 for the comparison group, aiming for a total of 65 events over the study period[63].

### Recruitment {15}

The study protocol was approved by the National Healthcare Group in Singapore, Domain Specific Review Board. There are four avenues of recruitment. The first is contacting participants from a previous pilot study conducted by the same research team in this protocol [64]. The second avenue is recruiting participants using snowball sampling (e.g. friends, family), the third is via electronic flyer invitation through corporate e-mails (National University Healthcare System (NUHS) and Agency for Science, Technology and Research (A*STAR)), and the fourth is advertising on social media (e.g. LinkedIn, Instagram, Facebook advertisements). Interested individuals will contact the study team via phone or e-mail. The study team will explain the study and answer any questions raised*.* Potential participants will be invited to attend a screening visit for informed consent and screening procedures. Those who are screened passed will be scheduled to attend baseline and midpoint visits (26/27 weeks), year 1, and follow-up visit periods in years 2, 3, and 4. All the participants will be able to provide written informed consent.

## Assignment intervention: allocation

### Sequence generation {16a}

A total of 400 women will be stratified and randomised based on prognosis factors to either group 1 (intervention) or group 2 (control) based on 1:1 allocation using R statistical software.

### Concealment mechanism {16b}

The allocation is concealed in that the allocation sequence is automatically generated in R software and simultaneous with the assignment.

### Implementation {16c}

The allocation sequence will automatically be generated in the Block Rand R software at the end of the baseline, and a screen will show participants to which group she has been assigned.

## Assignment of interventions: blinding

### Who will be blinded {17a}

Given the nature of the study design, blinding of participants and research personnel will not be possible. The study team will instruct the participants in the intervention and comparison groups to download the Apps, and each participant will be provided with a unique identification code.

### Procedure for unblinding if needed {17b}

In the case of high depression scores on the BDI, including item 9 (suicidal ideation) and anxiety on the STAI, the participant will be flagged and reported to research coordinators, who will contact the participant to provide additional referral and helpline resources in Singapore. Similarly, scores that reveal a potential developmental delay in the child measured by the ASQ-3 will be notified to the mother, and a referral will be made for further evaluation.

## Data collection and management

### Plans for assessment and collection of outcomes{18a}

The baseline, midpoint visit (26/27 weeks), 1-year visit, and 3-year follow-up assessments will be administered on-site through the Recap platform assisted by research coordinators. The REDCap will be used for all the measurements and will follow complex skip logic developed for this study, based on participants’ responses to reduce respondent burden and increase the completeness and accuracy of responses.

The intervention group randomised to the LvL UP App will collect objective and self-reported scales from the mHealth App throughout the intervention.

### Plans to promote participant retention and complete follow-up {18b}

Participants will be reimbursed for their time, inconvenience and transportation costs as follows: (a) screening visit — S$20; (b) completion of baseline study visit — S$80; (c) completion of midpoint study visit — S$40; (d) completion of year 1 study visit — S$80; (e) completion of level 1 to level 3 digital coaching sessions via LvL UP App (applicable to participants in intervention group) will be a total of S$120 and S$40 per level of completion; (f) completions for all three study visits, participants will be given an additional S$80 as bonus; and (g) completion of year 2, 3 and 4 yearly visit the participants will receive S$80 per visit. The research team will call the participants to remind them to attend the visits.

Additionally, the intervention group will receive reminders from the LvL UP App regarding the day and time of the coaching session and daily random lifehack from any of the pillars.

### Data management {19}

The Singapore Institute for Clinical Sciences (SICS) team will maintain a master dataset for all participants who were referred to the project for recruitment, along with a record of whether they withdrew before or after completing the screening and baseline measurements or after initiating the intervention, were considered ineligible for participation, or were terminated from the study or conducted the study. Protection of participant privacy concerning biological samples and questionnaire data will be achieved by assigning each participant a study identification number and then creating a separate de-identified file. Anonymised data from the participants will be shared between SEC and SICS through a secure AWS server. All data analyses will be carried out with the de-identified data file.

### Confidentiality {27}

Identifiable individual participant information obtained from this study is confidential, and disclosure to non-relevant third parties is prohibited. Participant confidentiality will be further ensured by assigning each participant a unique participant identification code for anonymised data entry and sample identification. All computer entry and networking programs will be done with coded numbers only.

## Statistical methods

### Statistical methods for primary and secondary outcomes {20a}

#### Analysis of aggregate intervention effects

The primary continuous outcome for the onset of diabetes will be analyzed with linear mixed models (LMM) with outcome measurement (at the three follow-up time points) as the dependent variable and based on the intention-to-treatment (ITT) principle.

Multiple linear regressions will determine the relationship between outcome measures and predictors, adjusting for potential confounders. Multiple linear regression analyses will estimate the effects between groups at the end point follow-up. Generalised estimating equations and mixed effect models will be used for longitudinal data analysis. A *p*-value of < 0.05 will be considered statistically significant. Correction for multiple tests will be performed. All statistical analyses will be conducted using the R program or STATA for Windows (Stata Corporation). The treatment effect within and between the two groups will be assessed using the Cohen *d* statistics [65].

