### Outcomes {12}

Table 1 shows the outcomes and timeline of the study. The primary outcome will be the onset of T2D/confirmed by a 2-h 75 g oral glucose tolerance test (OGTT) over a 4-year study period. OGTT will be done at the screening visit, year 1 visit, and follow-up visits in years 2, 3, and 4. Secondary outcomes include (a) onset of impaired fasting glucose and impaired glucose tolerance; (b) changes in cardiometabolic variables (body weight, HbA_1c_, insulin, blood lipids, blood pressure), and (c) changes in women’s body composition as assessed by bioelectrical impedance analysis (BIA). Secondary measures will be taken at baseline visits, middle point, year 1, and 2, 3, and 4-year follow-up period.

**Table 1 Tab1:** Outcomes and timeline

Assessments	Screening visit	Baseline visit	Midpoint visit (26/27 weeks)	Year 1 visit	Year 2 visit (follow-up)	Year 3 visit (follow-up)	Year 4 visit (follow-up) endpoint
Lab tests							
OGTT test	X				X	X	X
Height, weight and blood pressure measurements	X	X	X	X	X	X	X
Bio-sample collection: buccal swab, saliva, and stool samples		X		X			X
BIA		X		X	X	X	X
Fasting blood draw		X	X	X	X	X	X
Questionnaires							
Demographics	X			X			
GDM and family history of diabetes	X						
Spouse and child health	X			X			
Lifestyle and dietary	X			X			
Diabetes awareness	X			X			
14-day e-Diary recording		X	X	X	X	X	X
SF-36		X	X	X	X	X	X
STAI		X	X	X	X	X	X
BDI-II		X	X	X	X	X	X
CERQ		X	X	X	X	X	X
MEQ		X	X	X	X	X	X
PSQI		X	X	X	X	X	X
SHS		X	X	X	X	X	X
HLQ		X	X	X	X	X	X
PSS-4		X	X	X	X	X	X
WHO-5		X	X	X	X	X	X
Child-related questionnaires							
BISQ-R-SF		X		X			
CSHQ		X		X			
StimQ toddler/preschool		X		X	X	X	X
ASQ-3		X		X	X	X	X
BRIEF-2		X		X	X	X	X
BASC-3-BESS Parent Form		X		X	X	X	X
Questionnaires administrated within the LvLUP App (intervention group only)							
PHQ-4		x	x				
IPAQ-SF		x	x				
MFFQ		x	x				

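### The primary outcome is onset of T2D and the trial is sized on a hazard ratio, but the named primary analysis is a linear mixed model for a continuous outcome, to which the stated 80% power does not apply

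*Protocol article*

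**What the plan says.** Three parts of the protocol article bear on the primary comparison.

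- **Outcomes {12}**: "The primary outcome will be the onset of T2D/confirmed by a 2-h 75 g oral glucose tolerance test (OGTT) over a 4-year study period". The text adds that "OGTT will be done at the screening visit, year 1 visit, and follow-up visits in years 2, 3, and 4". Table 1 has no OGTT mark at year 1.
- **Sample size {14}**: the inputs are a control median survival of 6 years, a hazard ratio of 0.5, 3 years of follow-up, 20% censoring and 80% power. They give cumulative event rates of 0.22 and 0.12 and arms of 188 (comparison) and 189 (intervention), "aiming for a total of 65 events over the study period".
- **Statistical methods {20a}**: "The primary continuous outcome for the onset of diabetes will be analyzed with linear mixed models (LMM"). The model is to follow intention to treat and to use measurements from three follow-up visits, which the section does not identify. Without naming an outcome, it adds "Multiple linear regression analyses will estimate the effects between groups at the end point follow-up", general use of GEE and mixed models for longitudinal data, and Cohen's d as an effect measure both within and between groups.

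No Cox, log-rank or other survival method appears anywhere. Logistic regression for binary outcomes appears only under Interim analyses {21b}. The section on non-adherence and missing data {20c} describes a mixed model for total scores. Under the discontinuation criteria {11b}, a woman whom the study team diagnoses with T2D at a follow-up visit is removed after that visit. One diagnosed by her doctor in year 1 is invited to complete the endpoint measures and is then withdrawn.

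**The concern.** Onset of T2D is a yes/no event with a time attached, seen only at scheduled OGTT visits. A linear mixed model needs a continuous measurement repeated on each woman. Followed literally, the methods section would analyse some unnamed continuous variable (perhaps a glucose value) and report a difference in means. That is a different question from whether the app delays or prevents diabetes.

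Three things are at stake:

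- The power claim in the sample size section would not describe the primary test.
- The primary result would not be the hazard ratio for which the trial was designed.
- With the outcome and sizing pointing one way and the analysis another, the primary test could be settled after data are seen, in a trial where participants and research staff are not blinded.

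**Working it through.** **1. Which test does the sample size belong to?**

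Inputs from Sample size {14}: hazard ratio 0.5, power 80%, equal groups. The significance level is printed as 0.05%. I read it as two-sided 5%, because that reproduces the figures and the methods section uses p < 0.05. Taken literally, 0.0005 would need 156 events.

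Schoenfeld events = 4 × (1.960 + 0.842)² / (ln 0.5)² = 4 × 7.849 / 0.4805 = 65.35. The plan states 65.

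**2. Do the event rates and the sample size follow?**

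Control hazard λ = ln 2 / 6 = 0.1155 per year, and half that (0.0578) in the intervention arm. Take the 20% censoring as a hazard c = 0.2 per year and follow-up T = 3 years. The probability of an observed event is λ/(λ+c) × (1 − exp(−(λ+c)T)).

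- Comparison: 0.1155/0.3155 × (1 − exp(−0.9466)) = 0.224 (stated 0.22).
- Intervention: 0.0578/0.2578 × (1 − exp(−0.7733)) = 0.121 (stated 0.12).
- N = 65 / ((0.2240 + 0.1207)/2) = 377 (stated 189 + 188 = 377).

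The article does not say whether 20% is annual or total. Read as 20% in total over 3 years, the rates would be 0.26 and 0.14 and N about 319, so only the annual hazard reproduces the plan.

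Every stated figure is therefore that of a log-rank or Cox comparison. With 65 events that test has 79.8% power.

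**3. What power does the named analysis have?**

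The power of a linear mixed model needs a continuous variable, a mean difference, an SD and a within-woman correlation. The article gives none of these, so no figure can be computed and the 80% cannot be carried over.

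**4. What does removal after diagnosis do?**

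Under the plan's exponential assumptions, and before any loss to follow-up, the share of 4-year onsets that occur by year 3 is:

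- comparison: (1 − 0.5^(3/6)) / (1 − 0.5^(4/6)) = 0.2929 / 0.3700 = 79%;
- intervention: (1 − 0.5^(3/12)) / (1 − 0.5^(4/12)) = 0.1591 / 0.2063 = 77%.

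Women diagnosed by then supply no later measurements. A repeated-measures model thus has dropout caused by the outcome itself. A year-4 model confined to women still attending would lose those onsets.

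Simulated power, with 400 women and annual OGTT detection (3,000 to 4,000 replicates per run; ranges are across separate runs):

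| Analysis | Loss hazard 0.20/year | About 20% lost in total |
|---|---|---|
| Log-rank on all visits | 82–83% | 92–93% |
| Linear comparison of cumulative T2D status at year 4, diagnosed women kept as events | about 80% | 92% |
| Linear comparison at year 4, only women still in the study | 20–21% | 31–35% |

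The large loss comes from restricting the analysis to women still attending, not from using a linear model.

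**5. Would a matching analysis rescue the stated power?**

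Largely, yes. With 377 women, annual detection and the 0.2 per year loss hazard, a simulated visit-grouped log-rank test has about 73% power at 3 years (about 59 events) and about 81% at 4 years (about 69 events).

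**The case against.** The best defence is that a journal article condenses the plan and the SAP may name the right model. That would cover a missing detail, but here a specific analysis is stated and it conflicts with the stated outcome and sizing.

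A second defence is that the authors meant a mixed model on glucose. Then the primary outcome would be mean glucose, and both the Outcomes and the Sample size sections would be wrong instead.

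Other objections do stand, and they limit the point:

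- A reader might infer that the trial's real power is only 20–31%. The documents do not support that. The figure requires restricting the year-4 comparison to women still in the study, which the methods section does not state. The article claims intention to treat, and ending a woman's visits does not erase her known diagnosis.
- A reader might infer that none of the listed methods could address onset. A GEE with a binary outcome and a suitable link could estimate a discrete-time hazard ratio, and a linear model on cumulative status gives a risk difference. Neither is assigned to T2D, however, and the text says continuous.
- A reader might infer that the endpoint regression and Cohen's d are meant for T2D. The section covers primary and secondary outcomes and does not tie either to T2D. Both may be intended for weight, HbA1c or questionnaire scores.

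**Conclusion.** The primary analysis is wrong as written and must be corrected. The outcome is an event and the sizing is for a hazard ratio of 0.5 with 65 events, while the assigned model is for a continuous outcome and estimates neither a hazard ratio nor a risk of onset. The stated 80% power (79.8% on 65 events) holds for a log-rank or Cox test. It is undefined for the mixed model.

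Outcome-driven removal is a further weakness of any repeated-measures model. The 77–79% loss of onsets applies only to a year-4 analysis limited to women still attending.

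These conclusions rest on reading the significance level as two-sided 5% and, for the event rates, the censoring as 0.2 per year. The central mismatch depends on neither. The reference to three follow-up time points also needs reconciling with the four post-baseline OGTTs in the Outcomes text and the three in Table 1.

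**What to change.** Replace the opening sentence of Statistical methods {20a} with one named primary analysis, for example:

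*Onset of T2D from randomisation to year 4 will be compared by intention to treat with a discrete-time proportional-hazards model (complementary log-log link) for onset between scheduled OGTTs, adjusted for the randomisation strata. The hazard ratio will be reported with its 95% CI at a two-sided 5% level, with cumulative incidence by arm. Women removed after a T2D diagnosis count as events. A log-rank/Cox analysis is a sensitivity analysis.*

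In the same amendment:

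- State which visits carry an OGTT, and how the model treats an interval in which a visit was skipped for pregnancy.
- Keep mixed models, linear regression and between-group Cohen's d, but assign them explicitly to continuous secondary outcomes.
- Do not call a within-group d a treatment effect. It is change over time within one arm.

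The cost is an amendment to the protocol and SAP, notified to the ethics board when required. Recruitment has begun, so it should be dated and made before outcome data are examined by arm. It needs no new data or patients, and the stated sample size and event target can stand.

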### Intervention description {11a}

The comparison and intervention group will be assigned to holistic lifestyle mHealth interventions. The comparison group (Happy App and Oura ring) will receive only psychoeducation to promote a healthy lifestyle through the HAPPY App and sleep tracking using an Oura ring and associated App. The Happy App was developed by the Singapore Institute for Clinical Sciences (SICS); it encompasses only educational content on lifestyles based on resources from the Singapore Health Promotion Board, including information about diet intake, physical activity, sleep, and mental well-being. The HAPPY app also displays health outcome data collected during the study visits (e.g. body weight, blood pressure, fasting glucose, and 2-h 75 g OGTT). The Oura Ring is an activity-tracking wearable that monitors physical activity, sleep, and heart rate variability, which can be synced with the Oura App.

The intervention group (LvL UP App, Happy App, and Oura Ring) will receive the same Happy App, Oura Ring and Oura App, with the additional LvL UP App version 2.0. The LvL UP App has been developed by the Future Health Technologies Programme at the Singapore ETH-Centre (SEC) for iOS and Android. It is designed to be culturally relevant in Singapore and is based on evidence-based behavioural strategies [35]. A separate paper[35] describes the conceptual model, development process, and characteristics of LvLUP version 1.0. In this study, we will use an updated 2.0. version. The LvL UP App 2.0 is a smartphone-delivered holistic lifestyle intervention focusing on three core pillars: *eat well* (diet), *move more* (PA), and *stress less* (mental well-being), including sleep content in each pillar delivered through a coaching health and tools paradigm.

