### Methods in analysis to handle protocol non-adherence and any statistical methods to handle missing data {20c}

Intention-to-treat analysis will be used to examine trial efficacy. Total scores will be modelled using fixed effects of time, intervention group, interaction between time and intervention group, and a random effect of individual.

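### The plan calls within-arm change, measured by Cohen's d, a treatment effect; only the between-arm contrast is one (minor, wording)

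*Protocol article*

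**What the plan says.** In the Protocol article, the section on analysis of aggregate intervention effects (item 20a) ends its description of methods with: "The treatment effect within and between the two groups will be assessed using the Cohen" *d* statistic. The term for the effect covers both the within-group and the between-group quantity. Nothing elsewhere in the article restricts the within-group figure to description.

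Two other statements describe the randomised comparison. The same section says: "Multiple linear regression analyses will estimate the effects between groups at the end point follow-up". Item 20c, on non-adherence and missing data, says: "Total scores will be modelled using fixed effects of time, intervention group, interaction between time and intervention group, and a random effect of individual".

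The intervention description (item 11a) sets out what each arm gets. It opens: "The comparison and intervention group will be assigned to holistic lifestyle mHealth interventions". The comparison arm "will receive only psychoeducation to promote a healthy lifestyle through the HAPPY App and sleep tracking using an Oura ring and associated App". The intervention arm "will receive the same Happy App, Oura Ring and Oura App, with the additional LvL UP App version 2.0".

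**The concern.** The randomised question is what LvL UP adds to a package that both arms receive. Change from baseline inside one arm does not answer it. That change contains whatever would have happened over time anyway, any regression to the mean, and the effect of the HAPPY App and Oura ring, as well as any effect of LvL UP. In the comparison arm it contains no LvL UP effect at all, yet the sentence would give it the same name.

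The article describes other influences that act in both arms. The HAPPY App shows women their own weight, blood pressure and glucose results. Concomitant psychotherapy and drug treatment are allowed (item 11d). High BDI-II or STAI scores lead to referral or helpline information, and clinically significant, actionable blood findings lead to a referral letter (item 22). All of these could move a within-arm mean.

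What is at stake is interpretation. A published within-arm *d* for weight, HbA1c, BDI-II, STAI or PSQI, labelled a treatment effect, invites the reader to credit LvL UP with change that both arms share. The error can also run the other way: a shared deterioration would hide a real LvL UP effect.

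**Working it through.** **The plan's own figure.** The protocol states no expected value for Cohen's *d*, so there is none to reproduce. The sample size rests on a hazard ratio for onset of diabetes and does not bear on this point.

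**Inputs from the protocol (item 11a).**
- Comparison arm: HAPPY App, Oura ring and Oura App.
- Intervention arm: the same components plus LvL UP 2.0.

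**Inputs assumed for illustration.** The protocol gives no value for either.
- S: the change common to both arms (time trend, regression to the mean, shared components), in units of the outcome's SD, positive for improvement.
- L: the additional change due to LvL UP, in the same units.

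The same SD is used to standardise every quantity, and the effects are taken as additive.

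**Formulas.**
- Within-arm *d*, intervention = S + L
- Within-arm *d*, comparison = S
- Between-arm *d* = (S + L) − S = L

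**Results.**

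| S | L | Within intervention | Within comparison | Between arms |
|---|---|---|---|---|
| 0.2 | 0 | 0.2 | 0.2 | 0 |
| 0.2 | 0.2 | 0.4 | 0.2 | 0.2 |
| 0.3 | 0 | 0.3 | 0.3 | 0 |
| −0.2 | 0.2 | 0 | −0.2 | 0.2 |

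In the first and third rows LvL UP does nothing, yet both arms show a so-called treatment effect. In the second row the within-intervention figure is twice the true effect. In the last row a real effect disappears from the within-intervention figure. The between-arm column equals L in every row. The within-arm figure in the intervention arm is off by exactly S, whatever S is, so the conclusion that it is not a treatment effect does not depend on the values chosen.

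**Where the randomised contrast stands.** The same sentence provides for a between-group *d*. The end-point regression estimates differences between groups. In the model of item 20c, the time-by-group interaction is the between-arm difference in change. All three target L.

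**The case against.** The strongest reply is that this is loose wording about a supplementary statistic. The valid contrast is planned in three places, the trial is framed as a comparison of two arms (item 8), and the status of each effect size is the kind of detail an article may leave to a fuller document. Most of that stands, and it is why the point is minor. It does not remove the point: the sentence does not leave the status of the within-group figure open, but states it, wrongly.

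It is also fair to say that the size of any shared change is unknown. Item 6b argues that education alone is not enough to change lifestyles, which speaks against assuming a large S. The values above are illustrations, not forecasts.

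Two stronger readings are tempting, and the documents do not support either.

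- *A second route to a positive trial.* A reader might infer that within-arm change will be tested and used to claim efficacy when the randomised contrast is null. Suppose a paired test at 0.05, 151 women per arm (189 × 0.8), a baseline to follow-up correlation r of 0.5 to 0.7, and L = 0. The probability of a significant within-arm result is Φ(S/√(2(1 − r)/151) − 1.96). It is 0.23 to 0.35 at S = 0.1, 0.69 to 0.89 at S = 0.2, and 0.96 to 0.997 at S = 0.3. But Cohen's *d* is an effect size and not a test. The protocol names no paired test, no within-arm p-value and no decision rule tied to the within-arm figure. These probabilities describe a test that is not in the plan.
- *Cohen's d for the primary outcome.* The sentence sits under a heading that covers primary and secondary outcomes, so a reader might infer that *d* will be used for onset of type 2 diabetes. The sentence does not say so. How the primary outcome is modelled is a separate question and adds no weight here.

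**Conclusion.** Wrong as written, minor severity. A within-arm pre-post *d* is not a treatment effect in this trial, because the comparator's components are also part of the intervention arm. The figure for the intervention arm differs from the effect of LvL UP by the whole of the shared change, for example 0.2 against 0 under an assumed shared change of 0.2 SD and no LvL UP effect. That size rests on the assumed change, a common SD and additivity; the direction of the argument does not. The error is confined to the within-group effect size for continuous outcomes and its interpretation. It does not reach the sample size, the planned models or the randomised contrast.

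**What to change.** Reword the one sentence in item 20a. For continuous outcomes, define the treatment effect as the baseline-adjusted difference between arms with its 95% CI, and add a standardised version of that same contrast if wanted. State that change within each arm is reported descriptively, without p-values and without efficacy claims. The cost is one sentence. No new data, visits or change in sample size are needed, and the between-group methods already planned supply the estimate.
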